# Acetate Ringer’s solution versus 0.9% saline for septic patients: study protocol for a multi-center parallel controlled trial

**DOI:** 10.1186/s13063-020-05007-5

**Published:** 2021-01-25

**Keywords:** Sepsis, Septic shock, Acute kidney injury, Saline, Acetate Ringer’s solution

## Abstract

**Background:**

Previous study drew different conclusions on significant differences between saline and balanced crystalloid solution infused in critical illness but both showed a statistical difference in the sepsis subgroup. Thus, we will specifically focus on septic patients in this study to compare the effects of saline and balanced solution. We hypothesize that effects of saline on renal outcomes are related to the underline acute kidney injury (AKI) severity and total volumes of infusion.

**Methods/design:**

The investigators designed a pragmatic, multi-center parallel controlled trial recruiting 312 patients who are diagnosed with sepsis/septic shock in the intensive care unit (ICU) and will be assigned with either acetate Ringer’s solution or saline in the corresponding month. Patients with an end-stage renal disease (ESRD) or who need renal replacement therapy (RRT) prior to or at the time of enrolment are excluded. Enrolled patients will be regarded as with mild, moderate, or severe sepsis on the basis of the severity of their illness and will be divided into subgroups according to their initial renal function and various intravenous infusion volumes when being analyzed. The primary outcome is major adverse kidney events within 28 days (MAKE28), including the composite of in-hospital death, receipt of new renal replacement therapy, or persistent renal dysfunction. Secondary outcomes include 28-day mortality, internal environment disturbance, incidence and duration of vasoactive drug treatment, duration of mechanical ventilation, duration of RRT, and ICU and hospital length of stay.

**Results and conclusions:**

To our knowledge, this study will be the first to focus on septic patients and provide credible and evident data on the comparison of outcome between acetate Ringer’s solution and saline for intravenous infusion in adult septic patients on the basis of baseline renal function and infusion volumes taken into consideration.

**Trial registration:**

ClinicalTrials.gov NCT03685214. Registered on August 15, 2018

**Supplementary Information:**

The online version contains supplementary material available at 10.1186/s13063-020-05007-5.

## Background and rationale

Sepsis, a common problem in the intensive care unit (ICU) with high morbidity and mortality [1–4], is the main cause for acute kidney injury (AKI) in critically ill adults [5]. Septic AKI accounts for nearly half of all kinds of AKI [6] and increases mortality six- to eightfold [6, 7]. Fluid resuscitation plays a vital role in the treatment of sepsis and septic shock [8, 9], which attaches great significance to the type of solution infused during fluid management. Saline is not a “normal” fluid with high level of chloride which may be related to AKI and mortality [10, 11], but it is still commonly administered on a global basis so far [12]. Meanwhile, a preference for balanced crystalloid solution on venous transfusion is emerging [13, 14].

Until now, the choice of crystalloid for critically ill patients has not been confirmed [15, 16]. The SPLIT (Saline v Plasma-Lyte 148 for Intensive Care Unit Fluid Therapy) study conducted in four New Zealand ICUs [15] concluded with no difference neither in the primary outcome of the incidence of AKI nor in secondary outcomes of RRT use and mortality between the use of a buffered crystalloid and saline. However, this study was criticized for the relatively small volume of fluid as it may have been too low to cause detectable renal toxicity [16]. Another trial comparing saline to buffered crystalloid solutions (lactated Ringer’s solution and Plasma-Lyte A) in a single ICU, the SALT (Isotonic Solution Administration Logistical Testing) study, demonstrated no difference in the overall incidence of AKI or major adverse kidney events (MAKE30) including death from any cause, new receipt of renal replacement therapy (RRT), or persistent renal dysfunction within 30 observational days. However, notably, there was a difference on MAKE30 in septic patients who received larger volume of crystalloids in subgroup analysis. The study showed a dose-response relationship [16]. A recent multiple-crossover trial in critically ill adults in 5 ICUs demonstrated that the use of balanced crystalloids resulted in a lower rate of MAKE30 than the use of saline [17] though it showed no significant difference in the incidence of AKI and mortality respectively. It also showed difference in the sepsis subgroup, but the potential dose-response relationship related with infusion volumes in the subgroup was not clarified [18]. Both of the 2 studies implied that it is necessary to investigate further in septic patients as they are more prone to fluid damage. It still remains uncertain whether balanced crystalloid is superior than saline in septic patients, whether it is related to their initial renal function, and whether there is a dose-response relationship between fluids and outcomes. Thus, we carry out this study for further investigations.

## Objectives

This trial is the first to focus on septic patients and verify if acetate Ringer’s solution is superior to saline, especially in patients with septic AKI. It is aimed to provide credible and evident data and clarify if (1) there is a significant difference in the overall outcome between acetate Ringer’s solution and saline in septic patients, (2) the effect is dependent on the baseline renal function, and (3) there is a dose-response effect by subgroup analysis.

## Methods/design

The study is a multi-center, interventional, prospective, pragmatic [19], unblinded, and parallel controlled trial. This protocol is designed in accordance with the Standard Protocol Items: Recommendations for Interventional Trials (SPIRIT) guidelines [20]. All the data will be collected at each time spot as shown in the Standard Protocol Items (Fig. 1). The study flow is described in Fig. 2.

**Fig. 1 Fig1:**
[figure not shown]
Standard Protocol Items: Recommendations for Interventional Trials (SPIRIT) checklist. Baseline variables include baseline renal function, main diagnosis and complications, severity of illness at enrolment, demographic characters, and admission location. Intravenous fluid includes saline, acetate Ringer’s solution, and other fluids. Receipt of invasive support includes mechanical ventilation, receipt of RRT, and vasopressors. Clinical outcomes include vital status, vasopressor days, mechanical ventilation days, RRT days, ICU stay days, hospital length of stay and serum creatinine at hospital discharge

**Fig. 2 Fig2:**
[figure not shown]
Study flow. Abbreviations: RRT, renal replacement therapy; AKI, acute kidney injury; HUS, hemolytic uremic syndrome; ICU, intensive care unit

### Study sites and period

The study is planned to be conducted from March 1, 2019, to February 28, 2022, in 2 centers including the ICU of Zhongnan Hospital of Wuhan University and the ICU of Wuhan Central Hospital of Tongji Medical College, Huazhong University of Science and Technology. The above 2 hospitals are both tertiary hospitals integrating clinical, scientific research and teaching. Participating ICUs began enrolment sequentially over the first year of the study. Each ICU will enroll participants for an equal number of acetate Ringer’s solution and saline months for at least 12 months.

### Registration, ethical considerations, and monitoring

The study was registered on ClinicalTrials.gov before the participants’ enrolment started (identifiers: NCT03685214) (Table 1). This study follows the principles of the Helsinki Declaration 2013. The whole protocol has been reviewed and approved by the Ethics Committee of Zhongnan Hospital of Wuhan University (Clinical Ethical Approval No. 2018010) and the Ethics Committee of Wuhan Central Hospital of Tongji Medical College, Huazhong University of Science and Technology (Hospital Ethical Approval No. 201904). An independent data and safety monitoring board (DSMB) is monitoring the progress and safety of the trial. The DSMB is independent of the trial and is comprised of two academic intensivists, professor [name] and professor [name], who are experienced in the conduct of clinical trials in critical illness and outside the study, being able to pause the trial to investigate or give suggestions on potential safety issues to improve our design and implement. The DSMB follows the charter of the Ethics Committee of Zhongnan Hospital of Wuhan University.

**Table 1 Tab1:** Trial registration information

Data category	Information
Primary registration and trial identifying number	ClinicalTrials.gov NCT03685214
Secondary identifying numbers	None
Source(s) of monetary or material support	Wu Jieping Medical Foundation (Project identifier: HRJJ20171026)
Primary sponsor	Zhongnan Hospital of Wuhan University
Secondary sponsor	Wu Jieping Medical Foundation
Contact for public queries	[name]. PhD. [[contact]]
Contact for scientific queries	[name]. PhD. [[contact]]
Public title	Comparison of Balanced Crystalloids and Normal Saline in Septic Patients
Scientific title	Acetate Ringer’s solution versus 0.9% saline for septic patients: study protocol for a multi-center parallel controlled trial
Countries of recruitment	China
Health condition(s) or problem(s) studied	Crystalloid infusion for septic patients
Intervention(s)	Acetate Ringer’s solution versus saline
Key inclusion and exclusion criteria	Inclusion criteria:
	1. At the age of 18 to 80
	2. Diagnosed as sepsis (a possible or specific proof for infection plus Sequential Organs Failure Assessment (SOFA) scores ≥ 2)
	Exclusion criteria:
	1. Patients once having received RRT
	2. Patients requiring RRT prior to enrolment
	3. Patients possessed with only one kidney
	4. Patients with a medical history of renal transplant
	5. AKI caused by permanent kidney artery embolism or surgery injury to kidney artery
	6. AKI caused by glomerulonephritis, interstitial nephritis, or vasculitis
	7. AKI caused by postrenal obstruction
	8. Hemolytic uremic syndrome (HUS) or thrombotic thrombocytopenic purpura
	9. Patients having received fluid resuscitation over 1000 ml within 6 h prior to ICU
	10. Patients with serum chloride more than 120 mmol/L
	11. Pregnant women
	12. Patients enrolled into another clinical trial at the same time
Study type	Parallel controlled trial
Date of first enrolment	March 2019
Target sample size	312
Recruitment status	Recruiting
Primary outcome(s)	MAKE28
Key secondary outcomes	1. The occurrence of AKI
	2. Twenty-eight -day mortality
	3. Electrolyte disturbance, including hypernatremia, hyperchloremia, and hyperkalemia as well as hyponatremia, hypochloremia, and hypokalemia
	4. Changes of renal functions based on the biomarkers measured from the participants’ plasma and urine samples collected in the first 3 days after enrolment
	5. Other clinical outcomes: ICU stay, ventilator days, vasopressor days, and RRT days

### Participant patients

Participants’ inclusion criteria are as follows:
At the age of 18 to 80;Diagnosed as sepsis (a possible or specific proof for infection plus Sequential Organs Failure Assessment (SOFA) scores ≥ 2) [21].

Participants’ exclusion criteria are as follows:
Patients once having received RRT;Patients requiring RRT prior to enrolment;Patients possessed with only one kidney;Patients with a medical history of renal transplant;AKI caused by permanent kidney artery embolism or surgery injury to kidney artery;AKI caused by glomerulonephritis, interstitial nephritis, or vasculitis;AKI caused by postrenal obstruction;Hemolytic uremic syndrome (HUS) or thrombotic thrombocytopenic purpura;Patients having received fluid resuscitation over 1000 ml within 6 h prior to ICU;Patients with serum chloride more than 120 mmol/l;Pregnant women; andPatients enrolled into another clinical trial at the same time.

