### Study treatments

The intervention of treatment lies in fluid management. To exclude the possible difference caused by different balanced crystalloid solution, acetate Ringer’s solution is chosen for balanced crystalloid infusion. After patient screening and grouping, participants will be assigned with acetate Ringer’s solution or saline for intravenous infusion accordingly. The volume, infusion rate, and additive content (e.g., potassium chloride) of the fluid will be determined by responsible clinicians. The intervention will last for 5 days after patients’ enrolment. Other solutions are permitted to be used as carrier fluids for the infusion of any drug on the occasion when neither acetate Ringer’s solution nor saline is considered compatible. Medication use except fluids will not be restricted in the study.

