### Parallel control and allocation

Patients will be divided into 2 parallel groups: acetate Ringer’s solution versus saline. Crystalloids for enrolled patients are assigned according to the number of the month. Once assigned, the solution will be applied for the first 5 days during the patients’ stay in ICU. The assignment remains during change of month. The solution applied in the beginning month in each ICU is determined randomly by Excel2016 of Microsoft Office to make sure that stratified patient groups will be randomized to receive either acetate Ringer’s or saline solution, followed by a monthly rotation of fluids, so that any potentially observed difference in renal function is not due to other confounding factors such as use of nephrotoxic medication or contrast media. According to the Excel2016-generated random numbers, acetate Ringer’s solution will be applied in the odd month and saline will be applied in the even month both in the 2 centers. The random number table is operated by the primary investigator alone and clinicians are not involved in the process.

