### Primary analysis

The primary analysis will be an intention-to-treat comparison of the primary outcome of MAKE28 between the saline and acetate Ringer’s solution. A generalized linear mixed-effects model will be used including fixed effects (sex, age, body mass index, group assignment, principal diagnosis, crystalloids received prior to ICU, SOFA score, APACHE II score, mechanical ventilation status, vasopressor usage, etc.) and random effects. It is aimed to describe patients’ baseline characteristics and eliminate confounding factors.

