### Data collection and management

Patients’ demographic data, main diagnosis, comorbidities, assigned crystalloids, general vital signs, SOFA scores, APACHE II, infection indices, and indices of multi-organ function including renal function, respiratory function, cardiac function, etc. at the time of enrolment will be collected as baseline data. Clinical information including infection indices (white blood cell count, procalcitonin, etc.), organ function indices (renal function (creatinine, urea nitrogen, cystatin C, urine volumes, etc.), respiratory function (PO_2_/FiO_2_, ventilation situation, etc.), hepatic function (total bilirubin, etc.), and indices of internal environment (blood gas analysis) will be detected during the first 5 days in ICU, and treatments such as vasopressors, mechanical ventilation, RRT, and electrolyte supplement will be recorded. These data and infused volumes of the assigned fluids will be collected for at least 5 days or until ICU discharge. ICU stay days, vasopressor days, RRT days, and ventilation days will be counted during 28 days after enrolment. These data will be collected to assess and analyze primary and secondary outcomes. Besides, patients’ blood and urine samples within the first 3 days after enrolment will be collected and stored for testing possible biomarkers for identifying AKI at an early stage.

Patients’ information and clinical data will be collected from the Hospital Information System (HIS) of the hospitals involved in this study and recorded in the Case Report Format (CRF) by the trial manager or trained personnel. An electronic password-protected excel, which will be applied for statistical analysis, will be created to summarize the data of all participants. All the data will be accessed by only investigators and authorized personnel to monitor the completeness and authenticity of the table. The confidentiality is secured and all the data will be preserved for the purpose of a secondary analysis or investigations by the investigators. To protect patients’ privacy, their names will not appear on the CRF table. Every participant will only be recognized by their study ID.

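### Prior fluid is counted to ICU entry but the intervention starts at enrolment, so crystalloid given in the ICU before enrolment is in neither the named covariate nor the volume analysis

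*Protocol article*

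**What the plan says.** Two items deal with fluid given before the study, and both are tied to ICU entry:

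- Participant patients (repeated in Table 1) excludes "Patients having received fluid resuscitation over 1000 ml within 6 h prior to ICU".
- Primary analysis lists among the fixed effects "principal diagnosis, crystalloids received prior to ICU, SOFA score, APACHE II score". The list is open-ended, but no other prior-fluid term is named.

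Treatment is tied to enrolment. Parallel control and allocation says "Crystalloids for enrolled patients are assigned according to the number of the month", and Study treatments says "The intervention will last for 5 days after patients’ enrolment". The same allocation section also says "Once assigned, the solution will be applied for the first 5 days during the patients’ stay in ICU", which counts from a different starting point if read literally.

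On recording, Data collection and management says that "infused volumes of the assigned fluids will be collected for at least 5 days or until ICU discharge". The volume subgroup in Study outcomes is likewise defined on the assigned crystalloids. The Fig. 1 legend lists other fluids among the data collected, but the time grid is not shown.

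**The concern.** ICU entry and enrolment are two events, and nothing in the article makes them one. The abstract recruits patients diagnosed with sepsis in the ICU, which allows the diagnosis to come after entry. No criterion requires sepsis at entry or sets a window for enrolment. Whatever crystalloid a patient receives in between falls after the prior-fluid count has closed and before the study-fluid count has opened.

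Two analyses are exposed. The primary model adjusts for severity measured at enrolment alongside fluid measured at ICU entry, so the fluid covariate may not describe the patient who was actually assigned. The third objective asks for a dose-response effect, and Main secondary analysis groups patients by infused volume. A patient with much fluid in the interval and little afterwards would be placed in a low-volume group despite a high true load.

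**Working it through.** The article has no figure of its own to reproduce here. The check compares reference times and then looks at what would follow from assumed volumes.

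**1. Reference times**

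| Item | Section | Counted to or from |
|---|---|---|
| Prior-fluid exclusion | Participant patients, Table 1 | ICU entry |
| Prior-fluid covariate | Primary analysis | ICU entry |
| RRT exclusion ("Patients requiring RRT prior to enrolment") | Participant patients | Enrolment |
| Five-day intervention | Study treatments | Enrolment |
| Five-day fluid application | Parallel control and allocation | First days of the ICU stay |
| Baseline data, including SOFA and APACHE II | Data collection and management | Enrolment |
| Follow-up organ-function measures | Data collection and management | First five days in ICU |
| Initial renal function | Main secondary analysis | Enrolment |
| AKI stage and severity scores | Additional secondary analysis | Day of enrolment |

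**2. Do the two five-day statements agree?** Let d be the days from ICU entry to enrolment. Study treatments gives study fluid for 5 days from enrolment. Read literally, the allocation section ends it at ICU day 5, leaving 5 − d days. These are equal only if d = 0. With d = 1 the periods are 5 and 4 days. No section requires d = 0.

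**3. Effect on volume grouping (volumes assumed).** Let P be litres given in the ICU before enrolment and S litres of assigned crystalloid. The volume analysis sees S; the patient received P + S. The share counted is S/(P + S):

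- P = 0.5, S = 8: 8/8.5 = 0.94
- P = 1, S = 5: 5/6 = 0.83
- P = 2, S = 3: 3/5 = 0.60
- P = 3, S = 3: 3/6 = 0.50

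Rank order can also reverse. A patient with P = 4 and S = 2 received 6 L but is counted at 2 L. A patient with P = 0 and S = 4 received 4 L and is counted at 4 L. The first ranks below the second on counted volume and above on total volume. This does not depend on which crystalloid P was.

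**4. Effect on the contrast between arms (same assumed volumes, all prior fluid taken to be saline).** Table 2 gives chloride of 154 mmol/L for saline and 115 mmol/L for acetate Ringer's.

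Ratio of total chloride loads = 154(P + S) / (154P + 115S). With S = 4:

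- P = 0: 616/460 = 1.34
- P = 1: 770/614 = 1.25
- P = 2: 924/768 = 1.20
- P = 4: 1232/1076 = 1.14

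With S = 2 and P = 4: 924/846 = 1.09.

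Absolute difference = 154(P + S) − (154P + 115S) = 39S. With S = 4 this is 156 mmol at every value of P.

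The ratio falls as P rises, while the absolute difference does not move.

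**The case against.** The strongest reply is that the article treats ICU entry and enrolment as practically the same moment. The allocation section and Data collection and management both speak of the first five days in the ICU. If enrolment is that prompt, the interval is short and little fluid falls in it. This stands as a limit on size. It does not remove the mismatch, because the coincidence is implied in two places, stated in none, and not required by the eligibility criteria.

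A reader might go further and infer that unlimited, uncounted non-study fluid carries over and dilutes the comparison. The documents do not support that, for five reasons.

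- Dilution depends on the metric. The chloride ratio shrinks with prior saline but the absolute difference does not, and the article does not say that relative load drives the outcome.
- The volumes are all assumed, as is the type of fluid. The article does not say what fluid unenrolled ICU patients receive in an acetate month.
- No limit on volume is stated, but patients with serum chloride above 120 mmol/L are excluded, which removes some extreme saline loads. It limits a concentration and does not measure volume.
- Other fluids appear in the Fig. 1 legend and the covariate list is open-ended, so the data may be collected. What can be said is that this fluid is in neither the named covariate nor the stated volume analysis.
- A patient who becomes septic after a week in the ICU is not clearly eligible for treatment: on the literal allocation wording, no study fluid would remain to be given.

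It is also fair to say that volume of assigned crystalloid is a legitimate definition of exposure. That stands, but a dose-response reading of it still needs the preceding load in the model.

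**Conclusion.** The mismatch is real and stands in the text: prior fluid is counted to ICU entry, while assignment, the intervention and the other clinical baseline measures are tied to enrolment, with no stated window between the two. Fluid given in the ICU before enrolment is missing from the named covariate and from the volume analysis. The consequences are a possibly misstated baseline exposure in the primary model and possible misclassification in the dose-response analysis.

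The size cannot be computed, because neither the delay nor the volume is given. Under the assumed volumes in step 3, the counted share of a patient's crystalloid runs from 0.94 down to 0.50; with prompt enrolment it would be close to 1. Neither loss of power nor bias in a given direction is shown. The point is worth correcting because the third objective rests on volume and the correction is cheap.

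**What to change.** 1. Reconcile Participant patients, Study treatments, Parallel control and allocation, Primary analysis, and Data collection and management on the reference time. If enrolment is meant to coincide with ICU entry, say so; if not, state the permitted interval.
2. In the primary model, replace the covariate for crystalloid before the ICU with volume and type of crystalloid received before enrolment, over a fixed look-back that the sponsor specifies in advance.
3. Include the same pre-enrolment volume as a covariate in the volume (dose-response) analysis, keeping assigned volume as the exposure.

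The cost is one more field abstracted from existing charts and a revised covariate definition. No patient becomes ineligible. These changes improve adjustment and the reading of the volume analysis; they would not restore any contrast between arms that shared earlier fluid had removed. Whether the exclusion criterion should also be tied to enrolment is a trade-off against the pragmatic scope of the trial and is left to the sponsor. No volume limit is proposed here.
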